#### ***4.2.6 Physical activity and Exercise capacity***

##### ***4.2.6.1 Monitoring 24/7 physical activity***

The daily physical activity will be objectively tracked by FitBit watch technology. The FitBit watch will be also wired during night for measurements of the time asleep, restless and awake, Fitbit trackers help you understand each night to make the most of each day

##### ***4.2.6.2 Exercise capacity***

Participants will undergo exercise testing using a modified Balke treadmill protocol and continuous expired gas analysis. Resting and exercise vital signs will monitored continuously. The exercise duration and exercise-limiting symptoms will be recorded. The peak VO2, VCO2 and respiratory exchange ratio (RER) will be averaged over the last 15 seconds of the exercise test. The ventilatory equivalent (VE/VCO2 slope) will be calculated from start of exercise to the end of exercise.

#### ***4.2.7 Mitochondria function***

|                                                     |                                                        |                                        |
|-----------------------------------------------------|--------------------------------------------------------|----------------------------------------|
| Investigational Product
Hyperbaric chamber       | Short Title:                                           | Protocol No.
058-17-ASF             |
| Phase:
Investigator Initiated Phase
III study | Hyperbaric Oxygen Therapy for Fibromyalgia
Syndrome | Version, Date
Ver.4.0, 10 OCT, 2017 |

#### ***4.2.7.1 Mitochondrial oxygen consumption***

To monitor the consumption of oxygen and extracellular acidification in intact adherent lymphocytes, Seahorse Bioscience XFe96 Extracellular Flux Analyzer will be used (Seahorse Bioscience, North Billerica, MA, USA). For these experiments, lymphocytes will be seeded to  $3 \times 10^4$  cells/well in 12 wells (for each cell line) of XFe 96-well cell culture microplate (Seahorse Bioscience) in 200  $\mu$ L of DMEM and incubated overnight (14–16 h) at 37 °C in 5% CO2 atmosphere. After replacing the growth medium with 175  $\mu$ L of bicarbonate-free DMEM pre-warmed at 37 °C cells will be preincubated at 37 °C for 1 h for degassing before starting the assay procedure. Oxygen consumption rate (OCR) and extracellular acidification rate (ECAR) will be measured using mix/wait/measure times of 3/3/3 min. After baseline measurements of OCR and ECAR, OCR will be measured after sequentially adding to each well 25  $\mu$ L of oligomycin (1  $\mu$ M), carbonyl cyanide-ptrifluoromethoxyphenylhydrazone (FCCP) (0.25  $\mu$ M), and Rotenone/antimycin A (1  $\mu$ M) and ECAR by glucose (10  $\mu$ M), oligomycin (2  $\mu$ M) and 2-deoxyglucose (100  $\mu$ M) to the indicated final concentrations using the included ports on the XFe96 cartridges. Further analysis of these experiments will be performed as described [12]. Metabolic profile of the individual cell lines will be generated by plotting OCR against ECAR.

#### ***4.2.7.2 Measurement of mitochondrial potential***

Cells will be incubated with 3–3' dihexyloxacarbocyanine iodide [DiDOC6 (3)] (40 nm in Phosphate buffer saline +30  $\mu$ g mL Propidium iodide) (Molecular Probes, Eugene, OR, USA) for 15 min at 37 °C in the dark. Propidium iodide will be added to gate out dead cells. Cells will be transferred immediately to a tube on ice for analysis of the fluorescence intensity by flow cytometry (excitation 488, emission 525 nm)

### ***4.2.8 Immune system***

#### ***4.2.8.1 Inflammatory cytokines***

|                                                     |                                                        |                                        |
|-----------------------------------------------------|--------------------------------------------------------|----------------------------------------|
| Investigational Product
Hyperbaric chamber       | Short Title:                                           | Protocol No.
058-17-ASF             |
| Phase:
Investigator Initiated Phase
III study | Hyperbaric Oxygen Therapy for Fibromyalgia
Syndrome | Version, Date
Ver.4.0, 10 OCT, 2017 |

Blood Tests will include: IL-1, IL-6, Tumor necrosis factor-alpha, CRP.

#### ***4.2.8.2 Lymphocytes distribution***

Using a 4-color FACS the following tests will be performed: CD4 number, CD8 number, CD4:CD8 ratio, CD8+CD28null, Naïve B-Cells number, CD4CD25 positive number, NK numbers.

Isolation of peripheral blood mononuclear cells (PBMC) will be isolated using density gradient centrifugation and will be held 3 times in 1640 RPMI medium. Cells will be frozen in freezing medium and kept in liquid nitrogen until thawed for analysis.

PBMCs will be held twice in PBS with 3% FCS.  $1 \times 10^5$  cells will be re-suspended in 100 microliter PBS containing CD4, CD8, CD25, CD28, CD56, CD16, CD3 conjugated colored antibodies.

Total NK cell will be defined as the sum of CD56+CD16+CD3-, CD56-CD16+CD3- and CD56+CD16-CD3-. The total number of NK cells in the blood will be calculated by multiplying the % cells expressing the markers above and the total lymphocyte count in the blood.

#### ***4.2.8.3 Lymphoproliferative response***

Peripheral blood will be drawn at baseline and within 2 weeks after HBOT completion.  $6 \times 10^5$  PBMC will be suspended in 200 microliter RPMI 1640/10% FCS and incubated with either medium alone, 20microgram/ml PHA, PWM diluted 1:2  $10^3$  to induce suboptimal lymphocyte proliferative responses or 20 U/ml IL-2. PBMC will also be incubated for 7 days with medium or with ethanol inactivated candida antigen titrated to the lowest concentration inducing an optimal lymphocyte proliferative response. During the last 24 h cell will be exposed to 3H-thymidine. 3H-thymidine incorporation will be measured by a direct beta-counter.

PBMCs will be ashed twice in PBS with 3% FCS.  $1 \times 10^5$  cells will be resuspended in 100 microliter PBS containing CD4, CD8, CD62, CD28, CD45, CD3 conjugated colored antibodies

#### ***4.2.8.4 NK cytotoxicity***

|                                                     |                                                        |                                        |
|-----------------------------------------------------|--------------------------------------------------------|----------------------------------------|
| Investigational Product
Hyperbaric chamber       | Short Title:                                           | Protocol No.
058-17-ASF             |
| Phase:
Investigator Initiated Phase
III study | Hyperbaric Oxygen Therapy for Fibromyalgia
Syndrome | Version, Date
Ver.4.0, 10 OCT, 2017 |

NK cell cytotoxicity will be measured using K562 in c 51Cr release assay. PBMC (E) will be added in different concentrations to target cells (T). E/T cell ratios of 50/1, 25/1, 12.5/1 will be used. Each ratio will be incubated for 4 hours at 37 celsius. The plates will be centrifuged 10 mins, and 100microliter of supernatant will be transferred to new tubes and radioactivity will be determined. The spontaneous release will be measured by incubating target cells with medium alone. Maximum release will be measured by incubating target cells with 10% Triton X-100. The percentage of 51Cr release will be determined by  $\% \text{Lysis} = (\text{sample} - \text{spontaneous}) \text{ cpm} / (\text{maximum} - \text{spontaneous}) \text{ cpm}$ . The cytotoxicity per NK cell will be calculated as  $\% \text{Lysis} / (\% \text{NK cells} \times \text{number of effector cells total})$ . Index of cytotoxicity in the blood will be calculated as  $\text{number of NK cells in the blood} \times \text{cytotoxicity per NK cell}$ .

#### **4.2.9 Microbiome**

The Human Microbiome is the collection of all the microorganisms living in association with the human body. These communities consist of a variety of microorganisms including eukaryotes, archaea, bacteria and viruses. Bacteria in an average human body number ten times more than human cells, for a total of about 1000 more genes than are present in the human genome. However, because of their small size, microorganisms are only 1 to 3 percent of our body mass (that's 2 to 6 pounds of bacteria in a 200-pound adult). These microbes are essential for maintaining good health. For example, they produce some essential vitamins, extract nutrients from digested food, educate the immune systems to recognize dangerous invaders and even produce helpful anti-inflammatory compounds that might fight off other disease-causing microbes. (From the NIH Human Microbiome Project website: About the HMP).

##### **4.2.9.1 Microbiome and human behavior:**

The gut has been shown to have an effect on human behavior, while a broad spectrum antibiotic drug, Minocycline, has been recently suggested as a candidate treatment for depression [60] and schizophrenia [61]. Furthermore, an association between gastroenterological disease such as IBD and psychiatric morbidity (e.g. depression and anxiety) is well known, although precise mechanisms have not yet been shown.

|                                                     |                                                        |                                        |
|-----------------------------------------------------|--------------------------------------------------------|----------------------------------------|
| Investigational Product
Hyperbaric chamber       | Short Title:                                           | Protocol No.
058-17-ASF             |
| Phase:
Investigator Initiated Phase
III study | Hyperbaric Oxygen Therapy for Fibromyalgia
Syndrome | Version, Date
Ver.4.0, 10 OCT, 2017 |

Additionally, in a human study testing effects of probiotics on brain function, women receiving the probiotics had altered brain activity in regions associated with central processing of emotion and sensation [62]. Moreover, a pilot study conducted on 39 patients suffering from chronic fatigue syndrome demonstrated a significant decrease in anxiety symptoms among patients treated with *Lactobacillus casei* strain Shirota for two months, compared with placebo [63].

#### ***4.2.9.2 Gut-brain signaling:***

It has long been known that the brain has a strong effect on the gut. The gastrointestinal tract is sensitive to emotion in a way that anger, anxiety, sadness, and elation can all trigger gut symptoms. However, it has only recently been shown that the cross-talk between these organs is bilateral and the gut has effects on the brain as well. There appear to be different levels of signaling from the gut to the brain. One is neuronal - by bi-directional signaling, between the enteric nervous system (ENS) and the CNS via the vagus nerve. The ENS is composed of approximately 100 million nerve cells, leading to be called “our second brain”[64]. Additional indirect effects of the gut on the brain include altering function of the endocrine system. Microbes are capable of producing neurotransmitters such as norepinephrine, serotonin, and dopamine, which have effects on the CNS. Additionally, the microbiome can affect host hormone levels. Finally, it has been shown that the microbiome can affect immune system components, altering cytokine levels and levels of inflammation.

#### ***4.2.9.3 Microbiome evaluation method:***

Advances in bacterial genome sequencing is used for characterization of the human commensal bacterial community (microbiota) and its corresponding genome (microbiome). Using our cutting-edge facilities, 16S ribosomal RNA (rRNA) next-generation sequencing of fecal samples will be performed to identify bacteria present in the gut. 16S rRNA gene sequencing is a well-established method for studying phylogeny and taxonomy (the description, identification and evolutionary classification) of samples from complex microbial environments that are difficult to study. The test detects beneficial as well as pathogenic microorganisms associated with

|                                                     |                                                        |                                        |
|-----------------------------------------------------|--------------------------------------------------------|----------------------------------------|
| Investigational Product
Hyperbaric chamber       | Short Title:                                           | Protocol No.
058-17-ASF             |
| Phase:
Investigator Initiated Phase
III study | Hyperbaric Oxygen Therapy for Fibromyalgia
Syndrome | Version, Date
Ver.4.0, 10 OCT, 2017 |

specific infections, lifestyle choices, and gut conditions. To complete the picture of the gut ecology, the metatranscriptome (the complete mapping of messenger RNAs encoded by the organisms in a complex sample) will allow us to evaluate not only the identity of the specific organisms residing in the gut, but also their function.

|                                                     |                                                        |                                        |
|-----------------------------------------------------|--------------------------------------------------------|----------------------------------------|
| Investigational Product
Hyperbaric chamber       | Short Title:                                           | Protocol No.
058-17-ASF             |
| Phase:
Investigator Initiated Phase
III study | Hyperbaric Oxygen Therapy for Fibromyalgia
Syndrome | Version, Date
Ver.4.0, 10 OCT, 2017 |

## 5. Administration and regulation

### 5.1 Informed Consent

The investigator will obtain written informed consent from the parents of the patient participating in this study after adequate explanation of the aims, methods, objectives, and potential hazards of the study and prior to undertaking any study-related procedures. The investigator must utilize a consent form for documenting written informed consent. Informed consent will be appropriately signed and dated by the patient or the subject's legally authorized representative and the person obtaining consent.

### 5.2 Confidentiality

Subjects' anonymity will be strictly maintained and their identities will remain protected from unauthorized parties. The information is not to be disclosed to any third party (except for medical staff or employees or agents directly involved in the conduct of the study or as required by law).

### 5.3 Study Files

The medical records will be maintained adequately to enable good data storage and latter on management. Subjects' clinical source documents will include (but not limited to) the following: subject's hospital/clinic/ hyperbaric unit records, physician's and nurse's notes, appointment book, original laboratory reports, X-ray, MRIs, and special assessment reports, consultant letters, screening and enrollment log, etc.

### 5.4 Randomization and handling of the control group

Since the diversity of the patients included in the study, after signing the informed consent is expected to be high, no stratifies criteria will be used. Patients will be randomized in 1:1 fashion to either HBOT or pharmaceutical group.

|                                                     |                                                        |                                        |
|-----------------------------------------------------|--------------------------------------------------------|----------------------------------------|
| Investigational Product
Hyperbaric chamber       | Short Title:                                           | Protocol No.
058-17-ASF             |
| Phase:
Investigator Initiated Phase
III study | Hyperbaric Oxygen Therapy for Fibromyalgia
Syndrome | Version, Date
Ver.4.0, 10 OCT, 2017 |

## 5.5 Adverse Events

An adverse event (AE) is any untoward medical occurrence in a clinical investigation subject administered a medicinal product and which does not necessarily have a causal relationship with this treatment. An AE can therefore be any unfavorable and unintended sign, symptom, or disease temporally associated with the use of a medicinal product, whether or not considered related to the medicinal product. Pre-existing events, which increase in severity or change in nature during or as a consequence of use of a medicinal product in human clinical trials, will also be considered AEs.

Any medical condition or clinically significant laboratory abnormality with an onset date before the screening visit and not related to study procedures is considered to be pre-existing, and should be documented in the case report form.

|                                                     |                                                        |                                        |
|-----------------------------------------------------|--------------------------------------------------------|----------------------------------------|
| Investigational Product
Hyperbaric chamber       | Short Title:                                           | Protocol No.
058-17-ASF             |
| Phase:
Investigator Initiated Phase
III study | Hyperbaric Oxygen Therapy for Fibromyalgia
Syndrome | Version, Date
Ver.4.0, 10 OCT, 2017 |

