#### Log of Changes

| Date       | Description                                                    | By | Revision |
|------------|----------------------------------------------------------------|----|----------|
| 07.03.2017 | Original document                                              | SE | 1.0      |
| 07.03.2017 | Appendix documents                                             | SE | 2.0      |
| 05.09.2017 | Change of sub-investigators
Change 1.5ATA HBOT to 2ATA HBOT | SE | 3.0      |
| 10.10.2017 | Change PET-CT to SPECT                                         | SE | 4.0      |
|            |                                                                |    |          |
|            |                                                                |    |          |

|                                                     |                                                        |                                        |
|-----------------------------------------------------|--------------------------------------------------------|----------------------------------------|
| Investigational Product
Hyperbaric chamber       | Short Title:                                           | Protocol No.
058-17-ASF             |
| Phase:
Investigator Initiated Phase
III study | Hyperbaric Oxygen Therapy for Fibromyalgia
Syndrome | Version, Date
Ver.4.0, 10 OCT, 2017 |

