### 3. Methods

#### 3.1 Study population

The study will include 70 fibromyalgia patients in whom physical trauma, such as mTBI, could be considered as the trigger for FMS. Each participant will be examined at the time of recruitment and a diagnosis of FMS will be verified, based on the updated 2016 diagnostic criteria [40]. These criteria are based on the use of the widespread pain index (WPI) and the Symptom severity Score (SSS).

Exclusion criteria will include the presence of systemic inflammatory disorders including inflammatory rheumatological and autoimmune disorders. Patients suffering from active malignancy, chronic ongoing infection and major psychiatric disorders (excluding anxiety) will be excluded. Patients currently or previously treated with Duloxetine (Cymbalta) or Pregabalin (Lyrica) will also be excluded.

In the current study we will recruit patients not currently being treated with medications specific for FMS, including SSRI, SNRI, gabapentanoids and tricyclics, opioids and medical cannabis. Patients who are on such treatment will be required to discontinue treatment 2 weeks before recruitment.

In addition, patients who have one of the following criteria will also be excluded: Patients will be excluded if they will have one of the following criteria: had been treated with HBOT for any other reason prior to their inclusion; Chest pathology incompatible with pressure changes (including active asthma); Inner ear disease; Claustrophobia; Inability to perform awake brain MRI test; Previous neurologic conditions (eg. Epilepsy, neuromuscular diseases, metabolic diseases, etc.); Brain tumors; Skull base fractures; Active malignancy; s/p neurosurgery that included: ventricular drainage, subdural hematomas drainage, epidural hematomas drainage, intracerebral hemorrhage evacuation. Depressed fracture surgery, (Patients suffering from Encephalomalacia per MRI imaging will not be excluded). Inability to provide informed consent.

|                                                     |                                                        |                                        |
|-----------------------------------------------------|--------------------------------------------------------|----------------------------------------|
| Investigational Product
Hyperbaric chamber       | Short Title:                                           | Protocol No.
058-17-ASF             |

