### 3.2.1 HBOT protocol

A total of 60 daily hyperbaric oxygen treatment sessions will be administrated 5 days per week. Each session will include exposure of 90 minutes to 100% at 2 ATA, with 5 minutes air breaks every 20 minutes.

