## 6. Statistical Considerations

### 6.1 Analysis Sets

#### *6.1.1 Safety Analysis Set*

The safety analysis set will consist of all subjects with whom the study treatment was initiated.

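### Section 5.5 ties adverse events to a medicinal product although the tested product is a hyperbaric chamber; separately, Section 5.1 conflicts with itself and with Section 3.1 on who consents

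*Protocol*

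**What the plan says.** **Adverse events.** Section 5.5 defines an adverse event in three sentences.

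- The first covers "any untoward medical occurrence in a clinical investigation subject administered a medicinal product".
- The second covers signs, symptoms or disease "temporally associated with the use of a medicinal product, whether or not considered related to the medicinal product".
- The third brings in pre-existing events that worsen "during or as a consequence of use of a medicinal product in human clinical trials, will also be considered AEs".

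Study procedures are mentioned only once in that section, in the rule on what counts as pre-existing before screening. The page header, repeated throughout, gives the investigational product as "Hyperbaric chamber". Section 3.2.1 describes the experimental treatment as 60 sessions and specifies that "Each session will include exposure of 90 minutes to 100% at 2 ATA". Section 3.2.2 offers the control arm one of two licensed drugs. Section 6.1.1 states: "The safety analysis set will consist of all subjects with whom the study treatment was initiated".

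**Consent.** Section 5.1 opens with: "The investigator will obtain written informed consent from the parents of the patient participating in this study". Its last sentence has the form signed by the patient or a legally authorised representative. The exclusion criteria in Section 3.1 end with "Inability to provide informed consent". No age limit is given.

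**The concern.** The definition reads like drug-trial text carried into a trial whose experimental treatment is delivered by a device. It fits the control arm without difficulty. It does not clearly fit the arm under test. If site staff apply it as written, an ear, chest or claustrophobia-type event during a session might not be recorded, while any event in a patient on medication would be. The protocol itself recognises these risks: Section 3.1 excludes inner ear disease, chest disease that does not tolerate pressure change, and claustrophobia.

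Even-handed recording matters here because Section 2 says that HBOT must show a decisive advantage over standard care to justify the time and resources it takes. A record of harms that is fuller on one side would weaken that judgement.

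The consent wording is a separate matter. Three statements on who consents cannot all apply, and this is a basic participant protection.

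**Working it through.** No arithmetic decides this point, and the protocol gives no safety figure to reproduce. The check sets the sections side by side.

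**Step 1: what the definition reaches.**

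| Element of Section 5.5 | Condition | Control patient on drug | HBOT-first patient before any study drug |
|---|---|---|---|
| Sentence 1 | has been given a medicinal product | met | not clearly met |
| Sentence 2 | event associated in time with its use | met | not clearly met |
| Sentence 3 | worsening during or through its use | met | not clearly met |

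The entry for HBOT-first patients is *not clearly met* rather than *not met*, because the protocol does not say whether the oxygen breathed, or the imaging agents in Sections 4.2.3.1 and 4.2.3.2, count as medicinal products.

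**Step 2: does another section close the gap?** Section 6.1.1 says which subjects are analysed, not which events count. HBOT patients are therefore in the safety denominator, while their events may fall outside the numerator. No other section extends the definition.

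**Step 3: study procedures.** Heat-pain testing and cold-water immersion (Section 4.2.5.1) and treadmill exercise (Section 4.2.6.2) can also cause events. In a patient on study drug, such an event is associated in time with a medicinal product and is covered. In an HBOT-first patient before any study drug, coverage is again unclear.

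**Step 4: after crossover (Section 3.2.3).** Sentence 1 requires no causal link. A control patient who took a study drug and then moves to HBOT is still a subject who was given a medicinal product, so events after the switch are covered. The doubtful group is essentially the HBOT-first patients.

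**Step 5: exposure in that group.** Sections 3.1 and 5.4 give 70 patients randomised 1:1, so 70 / 2 = 35 HBOT-first patients. At 60 sessions each, 35 × 60 = 2,100 scheduled sessions. With the 29 per arm that Section 6.1.2.1 requires before its dropout allowance, 29 × 60 = 1,740. These are counts of planned exposure. The protocol gives no event rate, so they do not convert into a number of events missed.

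**Step 6: consent.** The opening of Section 5.1 names the parents. Its last sentence names the patient or a representative. Section 3.1 excludes anyone unable to consent, which presumes that patients consent for themselves. The first statement conflicts with the other two, and the representative route also sits badly with the exclusion. Because no age limit is stated, the conflict rests on these statements and not on an age criterion.

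**The case against.** The best defence is that this is borrowed wording that nobody would apply literally. Section 5.5 contains no rule that excludes HBOT events. The header calls the chamber the investigational product of a phase III study, Section 6.1.1 speaks of study treatment, and Section 5.3 lists hyperbaric unit records among the source documents. Oxygen, the gadolinium contrast or the SPECT tracer could each be read as a medicinal product, and then sentence 1 would reach HBOT-first patients too. On consent, the signature sentence gives a workable route, and Section 5.4 also assumes that patients enter the study after signing.

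Much of this stands, and it rules out several stronger readings that a reader might infer:

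- *All HBOT events are excluded, including those after crossover.* Sentence 1 covers control patients who took a study drug, and the status of oxygen and the imaging agents is left open.
- *The safety comparison between arms is biased.* The protocol specifies no such comparison; it defines a safety set and lists no safety endpoint.
- *About 2,100 exposures go unrecorded.* That figure counts scheduled sessions, not events.
- *Consent is invalid for all 70 patients.* That would follow only if the sentence on parents were applied in place of the signature rule, and the consent form is not available for review.

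What the defence does not do is amend the definition. Whether an HBOT event counts still depends on each reader's view of what a medicinal product is, and for the control drugs that question does not arise.

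**Conclusion.** The adverse event definition is wrong as written for this trial. It does not clearly cover HBOT-session or study-procedure events in HBOT-first patients, planned at about 35. Any resulting under-recording would tend to favour HBOT, because the comparator is plainly a drug. That is a risk from literal application, not a shown effect. Its size cannot be estimated from the protocol: it ranges from nothing, if staff record HBOT events regardless or treat oxygen as a medicinal product, to an unknown share of events in that group.

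The consent wording is a second, independent fault: an internal contradiction that needs reconciling, with no basis for concluding that any consent was defective.

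Neither is something a statistical analysis plan would normally settle; both are statements present in the protocol.

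**What to change.** **Section 5.5.** Replace each of the four references to a medicinal product with study treatment (HBOT or study medication) or study procedure, adjusting the grammar of the first sentence. State that the definition applies identically in both arms and both treatment periods.

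**Sections 5.1 and 3.1.** Reconcile the two on who gives consent. Correct the reference to parents unless minors are intended, and in that case say so in the eligibility criteria. Whether the representative route stays should be settled in the same step; the protocol as it stands does not decide it.

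**Cost.** Amendment wording and an instruction for the case report form. The one small downside is that more events may be recorded in the HBOT arm than under the present text. Sample size and the primary efficacy analysis are untouched.
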